### Primary outcome

The primary outcome is the development of a PPC within the first 14 post-operative hospital days. PPCs will be diagnosed with the Melbourne Group Scale (MGS) diagnostic scoring tool, which is reliable and valid following UAS and thoracic surgery [5, 8] and has high inter-rater reliability [64]. This tool has eight clinical criteria: four factors relating to symptoms and four to diagnostic markers (Table 5). A PPC will be diagnosed when four or more factors are present from midnight to midnight on one post-operative day.

**Table 5 Tab5:** MGS PPC diagnostic criteria with modifications*

Diagnosis confirmed when four or more of the following are present:
Clinical factors
• New abnormal breath sounds on auscultation different to pre-operative assessment • Production of yellow or green sputum different to pre-operative assessment • Pulse oximetry oxygen saturation (SpO_2_) <90 % on room air on more than one consecutive post-operative day • Raised maximum oral temperature >38 °C more than one consecutive day
Diagnostic factors
• Chest radiograph report of collapse/consolidation. *When a CXR has been taken but no report is available, a ward medical officer or a senior respiratory physiotherapist with more than 10 years’ experience will be asked to report • An unexplained WCC greater than 11 × 10^9^/L • Presence of infection on sputum culture report • Physician’s diagnosis of *pneumonia, URTI, or an undefined chest infection, or prescription of an antibiotic for a respiratory infection

* modification made to original criteria

Participants will be assessed prospectively and daily for a PPC by a blinded assessor until the seventh post-operative day. Thereafter, additional PPC assessments are performed only as clinically suspected until day 14 when there are signs or symptoms of respiratory system deterioration reported within the medical record. To reduce the potential for missing data, retrospective collection of PPC data from the daily medical record will be permitted when a patient or assessor is unavailable for PPC assessment. The proportion of retrospective assessments will be reported. Components will be collected via the patient’s medical record and pathology/radiology databases. Diagnostic components (chest X-ray (CXR), white cell count (WCC), sputum microbiology) are recorded only if results are available. All medical officers are masked to group allocation and these diagnostic tests are ordered only as clinically indicated, and not routinely for the purposes of the LIPPSMAck POP trial.

For this trial, modifications (* in Table 5) have been made to diagnostic criteria to ensure that respiratory therapy will not be withheld longer than necessary from patients who may have developed a PPC. A CXR can be verbally reported by a blinded senior respiratory physiotherapist or ward physician, rather than awaiting a radiologist report. When three factors (out of a possible eight) in the MGS PPC tool are present, the blinded assessor or ward physiotherapist will contact the surgical ward doctor and discuss the option of further diagnostic testing to rule in or out a PPC. Additionally, these patients will be assessed twice daily to monitor clinical criteria for any deterioration.

A positive diagnosis of a PPC will be confirmed by a blinded senior physiotherapist, and the participant will then receive respiratory treatment as determined by the ward physiotherapist.

### Secondary trial outcomes

Secondary outcomes (Fig. 2) are:Days of hospital length of stay (LOS). This is defined as the continuous time spent in any type of inpatient hospital service (acute care, sub-acute rehabilitation, and time at another hospital) from the day of admission to the day of discharge to a community dwellingICU LOS in days;Unplanned ICU admission at any time point during the acute stay;Pneumonia, defined as the presence of new CXR infiltrates along with at least two of the following criteria: temperature >38 °C, dyspnoea, cough and purulent sputum, altered respiratory auscultation, and WCC >14,000/ml or leukopenia <3000/ml [65] on any day within the first 14 post-operative hospital days;Time in hours from end of operation to time able to achieve ambulation greater than 1 min;Time in days from end of operation to post-operative day able to achieve ambulation greater than10 min;Time in days to discharge from physiotherapy service (Table 4) [62];Time in days to readiness for discharge from hospital as defined by standardised scoring criteria [66];Hospital costs for the UAS admission episode of care. This will be supplied by the participating centres’ or health departments’ costing data for each participant’s admission episode.Patient-reported complications at 6 to 8 weeks following day of surgery using a standardised semi-structured interview; andHRQoL using the SF-36 and functional capacity using SAQ [58, 67] at 6 to 8 weeks following day of surgery.

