### Statistical methods

The prognostic strength and size of imbalances to potential confounding baseline variables between groups will be assessed. Adjustment covariates will be selected by backward stepwise regression from covariates that may have the potential for clinically significant alterations in effect sizes. These include: history of a respiratory comorbidity, smoking history, self-reported physical activity levels, age, BMI, length in time of operation, operation category (upper gastrointestinal, colorectal, urological, other), ICU admission immediately following the procedure, incision type and location [72], intraoperative ventilation strategies [4, 73], fluid delivery [74], blood transfusions [75], mode of post-operative analgesia [76], and use of prophylactic antibiotics [50].

All outcomes are to be analysed using intention-to-treat. The absolute and relative rates of PPC in the trial groups will be estimated using multivariate robust random effects Poisson generalised linear regression to allow assessment of binary outcomes with or without adjustment for potential confounding variables (incidence rates and rate ratios, 95 % confidence intervals, *P*-values). Treatment centre will be treated as a fixed variable in the multi-level models. In addition, the effect of time from the end of surgery/anaesthesia to commencement of symptoms of PPC will be compared using Cox proportional hazards regression with and without covariate adjustment (hazards ratio, 95 % confidence intervals, *P*-values). Graphic representation of this analysis will be performed using the Kaplan-Meier method.

Binomial secondary outcomes, including pneumonia, unplanned ICU admission, and patient reported complications, will be analysed using mixed effects Poisson regression. Secondary outcomes with irregular distributions, including length of time periods (ICU and total post-operative LOS, time to ambulation for 1 and 10 min, and time to discharge from assisted ambulation physiotherapy service), HRQoL, and functional capacity, will be evaluated for group differences using mixed effects ordered logistic regression, with mean time (95 % CI) estimated for descriptive purposes using mixed effects linear regression, with or without log transformation depending on distribution. Hospital costs associated with the interventions will be compared using mixed effects linear regression. Log transformation of highly skewed cost data will be performed.

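### The pneumonia definition gives its white-cell limits per ml, a scale 1000-fold off that of Table 5; applied literally, any available count meets the criterion

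*Protocol article*

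**What the plan says.** The protocol article, under Secondary trial outcomes, has pneumonia "defined as the presence of new CXR infiltrates along with at least two of the following criteria". The list that follows is "temperature >38 °C, dyspnoea, cough and purulent sputum, altered respiratory auscultation, and WCC >14,000/ml or leukopenia <3000/ml". If cough with purulent sputum is taken as one item, that makes five criteria, with the white-cell item, "WCC >14,000/ml or leukopenia <3000/ml", satisfied by either a high or a low count.

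Table 5, under Primary outcome, uses a white-cell factor on a different scale: "An unexplained WCC greater than 11 × 10^9^/L". The text after Table 5 says that the diagnostic components of the primary outcome, white-cell count among them, "are recorded only if results are available", and that the tests are ordered on clinical grounds and not for the trial.

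Pneumonia is named in the Trial objectives and comes first among the key secondary outcomes in Table 1. It has its own model under Statistical methods: "Binomial secondary outcomes, including pneumonia, unplanned ICU admission, and patient reported complications, will be analysed using mixed effects Poisson regression". Nothing elsewhere in the article corrects or explains the per-ml unit.

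**The concern.** The two white-cell thresholds in one protocol cannot both be on the scale printed. The pneumonia limit should be the stricter of the two, since its numeral is 14 thousand against the equivalent of 11 thousand per microlitre. As printed it is lower by a factor of several hundred.

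The threshold decides who counts as a case in an analysed binary outcome. If it were applied as printed, the white-cell item would carry no information beyond the fact that blood was taken, and pneumonia would be diagnosed on weaker evidence than the rule intends. Extra false positives arising alike in both arms would be expected to pull a rate ratio towards 1. Data management also promises the database for independent analysis, so a third party who derives pneumonia from the printed definition could get different cases from the trial team.

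**Working it through.** **Inputs.** The upper and lower pneumonia limits, 14,000/ml and 3000/ml, and the decision rule come from Secondary trial outcomes. The comparison value, 11 × 10⁹/L, comes from Table 5. Conversions: 1 L = 1000 ml = 10⁶ microlitres.

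**Step 1: convert the printed limits.**
- Upper: 14,000/ml × 1000 ml/L = 1.4 × 10⁷/L = 0.014 × 10⁹/L.
- Lower: 3000/ml × 1000 ml/L = 3 × 10⁶/L = 0.003 × 10⁹/L.

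**Step 2: compare with Table 5.**
- 11 × 10⁹/L ÷ 1000 = 11,000,000/ml.
- 11,000,000 ÷ 14,000 = 785.7, so the Table 5 cut-off is about 786 times the upper pneumonia limit.

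**Step 3: read the same figures per microlitre.**
- 14,000 × 10⁶/L = 14 × 10⁹/L and 3000 × 10⁶/L = 3 × 10⁹/L.
- The change of unit is a factor of exactly 1000 and puts both limits on the Table 5 scale, with 14 above 11.

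**Step 4: apply both readings to a range of counts.**

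| Count (× 10⁹/L) | Same count per ml | Met as printed | Met per microlitre |
|---|---|---|---|
| 0.1 | 100,000 | yes | yes (low) |
| 2 | 2,000,000 | yes | yes (low) |
| 3 | 3,000,000 | yes | no |
| 7 | 7,000,000 | yes | no |
| 14 | 14,000,000 | yes | no |
| 20 | 20,000,000 | yes | yes (high) |

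As printed, every count in the table passes on the high limb, including very low ones, and none reaches the low limb.

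**Step 5: effect on the rule.** Take a participant with new infiltrates and a white-cell result. As printed, the white-cell item is always positive, so at least two of five becomes at least one of the other four. Read per microlitre, a count from 3 to 14 × 10⁹/L does not score, so two of the other four are needed. The readings therefore disagree only for participants with infiltrates, a count from 3 to 14 × 10⁹/L, and exactly one of the other four signs.

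**Step 6: illustration on assumed inputs.** The documents do not give the frequency of these signs. Assume, among patients with infiltrates and a result, that criteria are independent, each of the other four is present with probability p, and the white-cell criterion per microlitre is present with probability w.
- As printed: 1 − (1 − p)⁴.
- Per microlitre: w × P(at least 1 of 4) + (1 − w) × P(at least 2 of 4).
- p = 0.1, w = 0.1: P(at least 1) = 1 − 0.9⁴ = 0.344; P(at least 2) = 0.344 − 4 × 0.1 × 0.9³ = 0.052. Per microlitre: 0.1 × 0.344 + 0.9 × 0.052 = 0.081. As printed: 0.344.
- p = 0.4, w = 0.2: P(at least 1) = 1 − 0.6⁴ = 0.870; P(at least 2) = 0.870 − 4 × 0.4 × 0.6³ = 0.525. Per microlitre: 0.2 × 0.870 + 0.8 × 0.525 = 0.594. As printed: 0.870.

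Over p from 0.1 to 0.4 and w from 0.1 to 0.2, the share classified runs from 0.08 to 0.59 per microlitre and from 0.34 to 0.87 as printed. This shows the direction and possible scale; it is not an estimate for this trial.

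**The case against.** The strongest reply is that this is a self-evident slip. Read literally, every count is high and no count is low, which no clinician would accept. Table 5 of the same article gives the usual scale, and assessors score the primary outcome against it. If everyone reads the pneumonia figures per microlitre, classification is unaffected. That reply stands as to likely practical effect. It does not make the printed threshold right, and a definition of an analysed outcome should not depend on readers supplying the unit.

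A micro sign lost in text extraction would also produce this string. Other symbols (°, ×, ≥) survive in the text, so this is a caveat; a look at the published page would settle it.

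Several stronger readings are tempting, and the documents do not support them:
- A reader might infer that every participant meets the white-cell criterion. Only those with a result can, and the article says of the primary-outcome components that tests are ordered as clinically indicated and recorded when available.
- A reader might infer that one sign alone would make a pneumonia case. New infiltrates remain mandatory.
- A reader might infer that the electronic case report form codes the per-ml rule. Data management describes entry limits and prompts; it does not say that the form derives pneumonia or which unit it holds.
- A reader might infer that the pneumonia rate is in fact inflated, the treatment contrast diluted, or that sites classify differently. Each of these requires someone to have applied the text literally, and nothing in the article shows that.

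**Conclusion.** The pneumonia white-cell limits are wrong as printed when set against the protocol's own Table 5. They stand at 0.014 and 0.003 × 10⁹/L beside 11 × 10⁹/L, and a change of unit by a factor of 1000 restores consistency. Applied literally, they would over-classify pneumonia among participants with infiltrates and a white-cell result. The number affected cannot be sized from the document.

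The reach is one criterion of one secondary outcome. The primary outcome has its own white-cell factor on the usual scale, and the sample size does not depend on pneumonia. The conclusion that the slip is one of unit rests on the fit of the per-microlitre reading; the cited source of the definition was not available to confirm it.

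**What to change.** 1. Check the cited pneumonia definition, then restate both limits in the 10⁹/L units of Table 5. If the source is per microlitre, they become 14 and 3 × 10⁹/L.
2. Check whether the case report form, or any of the three sites, applied the per-ml limits.
3. If any did, re-derive pneumonia from the stored white-cell values, for all participants and by one rule, before the analysis. If none did, record that and stop at the wording.

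The cost is a correction of wording and one check. Any re-derivation would use data already held, provided the numeric counts were stored. Trial status reports that enrolment was still under way, so this can be settled before the outcome is analysed.

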**Fig. 2 Fig2:**
[figure not shown]
LIPPSMAck POP participant timeline and schedule of events. Describes LIPPSMAck POP participant timeline and schedule of procedures. Abbreviations: POD postoperative day, D/C discharge, DB&C deep breathing and coughing, RAPA Rapid Assessment of Physical Activity, PPC postoperative pulmonary complication, ICU intensive care unit, LOS length of stay, HRQOL health-related quality of life, SAQ Specific Activity Questionnaire

Post-hospital discharge follow-up of self-reported complications, SF-36, and functional capacity will be via phone interview with a site investigator at 6 weeks from the date of surgery. If patients are unable to be contacted by phone for a period of five consecutive working days, a standardised cover letter, questionnaires, and self-addressed return paid envelope will be posted to the participant. Forms not returned within 2 weeks of posting will be considered lost to follow-up for the post-discharge secondary outcomes.

## Data collection

### Pre-operative variables

To measure baseline characteristics the following variables will be collected directly from the patient or the medical record: centre of recruitment, age, gender, height (cm), weight (kg), body mass index (kg/cm^2^), planned surgical procedure, category (hepatobiliary/upper gastrointestinal, colorectal, renal and urology, vascular, or other) and reason for the procedure, physical health status according to the American Society of Anaesthesiologists (ASA) and rated by the attending anaesthetist at the PAC (score 1 to 5), chemotherapy during the preceding 6 weeks, presence of a nasogastric tube before operation, respiratory status (auscultation signs and patient report of a daily productive cough), cough strength and presence of sputum (patient is asked to cough forcibly, the physiotherapist makes a subjective scoring of strength, effectiveness, and presence of sputum), sputum class (mucoid, mucopurulent, purulent) and colour using a validated colour chart tool [68] of any observed or patient reported regularly produced bronchial secretions, patient-reported history of a chest infection in the previous 14 days and if antibiotics had been prescribed, smoking history (non-smoker, current smoker, or ex-smoker having ceased more than 8 weeks pre-operatively), smoking pack years (1 pack year = 20 cigarettes per day for 1 year), years since smoking cessation, SpO_2_ (%) on room air, heart rate (beats per minute), co-morbidities as documented in the medical record (history of stroke or any other type of debilitating neurological disease, diabetes, arthritis, osteoporosis, asthma, COPD or other type of chronic respiratory disease, history of an acute myocardial infarct or angina, peripheral vascular disease, upper gastrointestinal disease such as reflux or gastric ulceration, current depressive illness or anxiety/panic disorder, visual or hearing impairment), patient’s self-report if the listed comorbidities significantly limit their walking on a day-to-day basis, Functional Comorbidity Index score [69], HRQoL with the SF-36, patient-reported estimated maximum metabolic equivalent (MET) physical activity using a self-rated physical Specific Activity Questionnaire (SAQ) [58], patient-reported measure of physical activity status using the Rapid Assessment of Physical Activity (RAPA) questionnaire and categorised to sedentary, under active, under active regular light activities, under active regular, and active [57], patient-reported maximum walking time along flat ground at comfortable walking pace, any limiting factor for mobilisation, and maximum grip strength as measured on the dominant hand using a calibrated hand dynamometer (Jamar Plus+; Sammons Preston, Rolyon, Bolingbrook, IL) performed with patients seated with shoulders adducted, elbows flexed to 90°, and forearms in the neutral position. The dynamometer handle position will be set to the second position for all tests [70], and three tests will be performed with verbal encouragement with the best test result recorded.

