### Sample size

Sample size was calculated using inference for proportions comparing two independent samples with a 0.05 two-sided significance level and will have 80 % power to detect a 10 % absolute difference in PPC between Pre-Op (estimated at 10 %) and an education booklet (estimated at 20 %) when the sample size is 398. This is further increased by 11 % to account for attrition, resulting in a final sample size of 441.

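### Pre-operative maximum walking time is collected, but the analysis of time to ambulation >10 min does not secure it as a covariate

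*Protocol article*

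**What the plan says.** The Protocol article lists among its Pre-operative variables "patient-reported maximum walking time along flat ground at comfortable walking pace". It is collected as a baseline characteristic, and the Statistical methods section does not mention it.

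Two secondary outcomes concern walking after surgery: hours to ambulation >1 min, and "Time in days from end of operation to post-operative day able to achieve ambulation greater than10 min" (Secondary trial outcomes). Time to early ambulation is also a secondary objective (Trial objectives), and Table 1 lists the day of walking >10 min as a key secondary outcome. The education session itself sets a walking target beyond 10 min (Intervention group).

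Under Statistical methods, time to ambulation for 1 and 10 min is among the outcomes that "will be evaluated for group differences using mixed effects ordered logistic regression". That sentence names no covariate. Adjustment is mentioned explicitly only for the PPC models. The one general covariate rule in the section is backward stepwise selection from candidates introduced as an open list. That list contains self-reported physical activity levels and several surgical and peri-operative factors, but not walking time. Centre is to be a fixed variable in the multi-level models.

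**The concern.** The >10 min milestone is a walking-duration threshold, and the trial already holds a pre-operative measure of walking duration. Eligibility (Table 1; Eligibility and exclusion criteria) screens out only those who cannot manage about 1 min, so people with a usual maximum between about 1 and 10 min can be enrolled. For them the time to reach the milestone plausibly reflects pre-operative capacity as well as recovery and treatment.

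A plan that merely left the covariates for later would be no cause for comment. Here the article fixes a data-driven rule, under which even a listed candidate can be dropped. Randomisation and allocation describes blocking and names no stratification by walking ability, so the design does not balance this variable either. At stake is some power in a key secondary comparison, and room for choosing the adjustment after the data are seen.

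**Working it through.** **1. The plan's own figure.** The sample size section uses a "0.05 two-sided significance level" and claims "80 % power to detect a 10 % absolute difference in PPC" "when the sample size is 398". With rates 0.20 and 0.10, mean rate 0.15 and equal arms (assumed):

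n per arm = [1.960 × √(2 × 0.15 × 0.85) + 0.8416 × √(0.20 × 0.80 + 0.10 × 0.90)]² / 0.10² = (0.990 + 0.421)² / 0.01 ≈ 199, total 398.

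This reproduces the plan exactly, and 398 × 1.11 = 441.8 agrees with the stated 441. The calculation concerns PPC only. The article gives no power figure for time to ambulation, so 398 serves below only as the number analysed.

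**2. Is walking time secured?** There are two readings of Statistical methods for the ambulation outcomes. If their sentence is taken alone, no baseline covariate enters. If the stepwise rule extends to them, walking time is unnamed, and its nearest relative, physical activity level, may be eliminated. Neither reading guarantees it.

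**3. Is it a ceiling?** No. Standardisation of post-operative procedures allows walking in intervals with rest up to equal length, and the stage reached is total walking time without the rests. Someone with a 5 min maximum could walk three bouts of 4 min and record 12 min. The value is a plausible predictor, not a bound.

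**4. Size of the gain.** The correlation r between baseline walking time and the (latent) outcome is not in the documents; 0.1 to 0.5 is assumed. As a guide, adjustment multiplies the residual variance by (1 − r²). With 199 per arm, the standardised difference giving 80 % power unadjusted is (1.960 + 0.8416) × √(2/199) = 0.281. Adjusted power is Φ(2.80 / √(1 − r²) − 1.96), and equivalent N is 398 / (1 − r²).

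| Assumed r | 1 − r² | Power | Equivalent N |
|---|---|---|---|
| 0 | 1.00 | 80.0 % | 398 |
| 0.1 | 0.99 | 80.4 % | 402 |
| 0.2 | 0.96 | 81.6 % | 415 |
| 0.3 | 0.91 | 83.6 % | 437 |
| 0.4 | 0.84 | 86.3 % | 474 |
| 0.5 | 0.75 | 89.9 % | 531 |

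**5. Check in the planned type of model.** Step 4 is a linear approximation, so simulated ordered logistic models (without the random effects) were fitted: 398 participants, six categories, 300 runs per setting, Monte Carlo error about 2 points. Power without and with the covariate was 83 % v 86 % at r = 0.2, 78 % v 81 % at r = 0.3, and 84 % v 92 % at r = 0.5. The direction and rough size agree with the table.

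**6. Where the gain appears.** In a further simulation (199 per arm, seven categories, 150 runs per setting), the mean standard error of the treatment log odds ratio, unadjusted v adjusted, was 0.177 v 0.178 at r² = 0.05 to 0.10, 0.177 v 0.179 at 0.20, and 0.177 v 0.181 at 0.30. The interval does not narrow. Power rises because the conditional odds ratio lies further from 1. At r² = 0.01 the same simulation gave power of 0.80 v 0.79, that is, no gain.

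**The case against.** The strongest reply is that the covariates of a secondary model are usually left to the analysis plan, that dozens of baseline variables are recorded, and that the same complaint could be made about many of them. The candidate list is open, includes a related activity measure, and follows a commitment to assess the prognostic strength and imbalance of baseline variables. Operation category, incision type and mode of analgesia, all listed, may drive recovery time more strongly. The outcomes are elapsed hours and days, not walking capacity.

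Much of this stands. Adjustment along this dimension is not excluded, and nothing in the documents shows walking time to be the best predictor. The reply does not meet the central point: the article states a selection rule, and under that rule the inclusion of this variable depends on the data. Adjusting after seeing an imbalance is data-driven too.

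A reader might infer that baseline walking time caps, or nearly determines, whether a participant reaches 10 min. The rules on rests and summed walking time contradict that. For the >1 min outcome, eligibility already screens on about that capacity, so little limiting effect should remain.

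**Conclusion.** The point holds as a modest improvement to a secondary analysis. A directly relevant baseline value is collected, people with a maximum of 10 min or less can be enrolled, and the stated method does not secure the variable in the >10 min comparison. For >1 min the case is weak.

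The size rests wholly on an assumed correlation and on an effect chosen to give 80 % power unadjusted. The gain is negligible at r = 0.1 to 0.2, and power reaches about 84 to 90 % at r = 0.3 to 0.5. The documents do not say where r lies, or how many participants have a baseline maximum of 10 min or less.

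Two stronger readings are tempting and unsupported. One is that precision is certainly being lost in the form of a wider interval: r is unknown, and in ordered logistic regression the gain is power for a conditional odds ratio. The other is that the comparison is biased: randomisation prevents systematic bias, and only chance imbalance remains. The primary analysis and the sample size are unchanged.

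**What to change.** Add one sentence to Statistical methods: the model for time to ambulation >10 min will include pre-operative maximum walking time, on the log scale, as a fixed covariate, whatever the stepwise procedure selects. Doing the same for >1 min is optional. Keep centre as already planned. Report by arm the number of participants with a pre-operative maximum of 10 min or less.

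No new data are needed. The cost is one degree of freedom among about 400 participants, a few missing baseline values to impute, and an odds ratio that is conditional on baseline walking time and should be labelled so. If r proves small, little is gained and little is lost.
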